**Bladder or Ureteral Injury**				
**Bowel Injury**				
**Diaphragmatic Injury**				
**Gynecological Injury (ovaries, fallopian tubes, uterus, vaginal canal)**				
**Hepatobiliary Injury**				
**Hip Fracture**				
**Male Genital Injuries**				
**Pancreatic Injuries**				
**Pelvic Fractures–Major** ^**b**^				
**Pelvic Fractures–Minor** ^**c**^				
**Renal Injury**				
**Retroperitoneal Injuries**				
**Spinal Injuries–Unstable or with neurological compromise**				
**Spinal Injuries–Stable and with no neurological compromise**				
**Splenic Injuries**				
**Vascular Injuries–Aorta**				
**Vascular Injuries–Pelvic Vessels**				
**Vascular Injuries–Other Vascular Injuries**				

^a^Classification—Injury categories

No injury = No injury evident on A/P CT imaging

Clinically Insignificant injury = Unimportant injury that could be missed without significant consequences

Clinically Minor = Injury that may not require therapy, but is important to diagnose

Clinically Major = Injury that is associated with diagnostic and therapeutic implications

^b^Excludes minor avulsion injuries and non-displaced anterior ring fractures

^c^Minor fractures and non-displaced anterior pelvic ring fractures

**Interventions include:** Surgical intervention; Fracture reduction, repair or stabilization; Interventional radiology procedures or embolizations; Administration of blood or blood products; Reversal of anticoagulation; Administration of pressors

### Global assessment of potential missed injuries

For patients enrolled in the study and admitted as inpatients, hospital discharge summaries will be reviewed in order to determine whether any SAPI were missed by the initial ED evaluation. We will also review trauma, surgery and mortality logs, and quality improvement records to identify any cases of SAPI that were missed on initial presentation (including patients enrolled in the work-up bias assessment), and whether the involved patients underwent A/P CT imaging.

### Data storage and confidentiality

Temporary study index numbers will be assigned to each patient in order to link radiographic results and procedural interventions to survey data via the following procedure. At the time a radiographic request is made, the patient’s medical record number and study index number will both be recorded by a research assistant. The information in this file will be only available to the site principal investigators, and will be password protected. This file will contain no additional patient data or identifying information. The survey information for each patient will be stored in a separate secure file, and will be indexed by the assigned study numbers. This file will not contain any identifying patient information or links to individual patients. Once the radiographic and interventional results have been collected for a given patient, the study coordinators will examine the computer data file containing patient medical record numbers and ascertain the corresponding study index number. Radiography reports and outcomes will then be copied and labeled with the study index number, effectively redacting all identifying information from the report. The relabeled photocopies and outcomes will then be forwarded to a central repository for concatenation with the study survey data. At the completion of the study, the data linking each patient’s medical record and study index number will be deleted from each site’s encrypted database.

### Data analysis

The final concatenated database will be reviewed at the close of the study. Cases lacking radiographic reports or intervention outcomes will be deleted from the final data analysis.

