### Data collection

Our collected data will include patient demographic information (date, time, age, sex, and race) and the presence or absence of each individual study variable. Each record will also carry embedded information indicating the identity of the institution producing the data. Because we want to increase the external validity of the study to reflect general practice, we will not provide rigid definitions for any of the individual data elements. This will help ensure that the validated low-risk criteria are widely applicable; clinicians will be asked to judge whether these elements are present on the basis of their routine clinical assessment, as they would when eventually applying the decision instruments. However, for purposes of clarification, we will provide clinicians with general descriptions of each clinical characteristic. These will be presented as informational material to all sites and will be reviewed with clinicians during in-service training sessions conducted before the beginning of the study. Potential predictor variables have been selected according to *a priori* determined associations with SAPI and acceptable inter-rater reliability [8, 17, 21, 42–45]. Additional demographic, historical, vital sign, imaging, and outcome data will also be collected (S1 File presents our data collection instrument for candidate criteria).

Our study will also collect A/P CT imaging and outcome results for each patient. All patients will have received A/P CT imaging, and may have received plain pelvic imaging. These initial studies may be supplemented by any other imaging studies deemed necessary by clinicians involved in the patient’s care.

Clinical radiologist at each site will review the x-ray and CT images and prepare final radiographic reports. We will review the final radiographic interpretations to determine whether an individual has sustained a SAPI, but will classify injuries as major, minor, or insignificant based on review of procedural records.

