#### Validation of the A/P CT decision instruments

The validation phase of the study will involve the collection of the combination of clinical variables forming the A/P CT decision instruments [17]. A case will be considered true-positive if the patient has at least one of the variables and is given a diagnosis of SAPI based on the designated imaging modality. Cases of patients given a diagnosis of SAPI but in whom none of the variables are present will be classified as false-negative cases. Cases of patients with none of the variables and no SAPI will be classified as true-negative cases. The remaining cases will be classified as false-positive cases. These values will be used to calculate point measures and 95 percent confidence intervals (CIs) for sensitivity, NPV and specificity of the decision instruments.

We will consider an instrument to be adequately validated if the lower confidence intervals for sensitivity and negative predictive value exceed 98%.

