### Sample size calculations for derivation and verification studies

To be clinically reliable, the combined selective criteria must satisfy two requirements. First, patients identified as risk free by the decision instrument must never harbor injuries of major clinical significance. This is equivalent to requiring the instrument to have a 100% negative predictive value. Second, every patient with blunt trauma with an injury of major clinical significance must exhibit at least one of the risk criteria. This requirement implies that the sensitivity of decision instrument be 100%.

Verifying negative predictive value and sensitivity at an absolute level is not statistically possible with a finite sample size. However, it is possible to estimate limits for the true values of these proportions using exact statistical relationships. The lower confidence limit of a proportion (such as negative predictive value or sensitivity) is related to the total size of the study population. The quantitative relationship is expressed by the following equation from Fleiss [47]:

$$P_{L}=\frac{X}{X+(N‐X+1)\cdot F_{\frac{\alpha }{2},v_{1},v_{2}}}$$

Where:

P_L_ = Lower confidence limit for the proportion being studied (i.e. the lower confidence limit for the negative predictive value or sensitivity of selective criteria).

X = Number of times the event of interest is observed.

N = Total number of observations.

α = Statistical confidence value (Set to 0.05).

ν_1_ = Degrees of freedom for the numerator; ν_1_ = 2 [N—X + 1]

ν_2_ = Degrees of freedom for the denominator; ν_2_ = 2 X

F_α/2,ν1,ν2_ = One tailed value of the F-distribution with ν_1_ and ν_2_ degrees of freedom.

Validating a given P_L_ to a 95% level of statistical certainty implies that α = 5% (or α = 0.05). The main hypothesis of this study states that selective criteria will detect all injuries of major clinical significance in patients with blunt trauma without missing any such injuries. Thus, for purposes of sample size calculations, for either negative predictive value or sensitivity, the event of interest (presence of one of the risk criteria) should occur with every observation. Hence, X = N.

The degrees of freedom for the numerator and denominator are then given by:

ν_1_ = Degrees of freedom for the numerator; ν_1_ = 2 [N—X + 1] = 2 [N—N + 1] = 2

ν_2_ = Degrees of freedom for the denominator; ν_2_ = 2 X = 2 N

The expression for the lower confidence limit then becomes:

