$$P_{L}=\frac{N}{N+(N‐N+1)\cdot F_{0.025,2,2N}}=\frac{N}{N+F_{0.025,2,2N}}$$

Practical concerns regarding radiographic charges and radiation health effects suggest that selective criteria will still remain cost effective and reduce mortality and morbidity even when missing 2 out of every 100 injuries. This implies that negative predictive value need only be verified to a 98.0% lower confidence level, or equivalently, P_L_ = 0.98. Substituting this value in the lower confidence limit equation yields an algebraic equation for our injury population size, with a solution of N = 317. Thus, to confirm that the decision instrument has a negative predictive value of at least 98.0%, the study must enroll 317 blunt trauma patients who have none of the risk criteria, and none of whom have injuries of major clinical significance. Since approximately 10% of victims of blunt trauma are free of the risk criteria, this derivation would require a population of 3,170 patients with blunt trauma. Unfortunately, confirming that the instrument has 98.0% sensitivity requires studying 317 patients having injuries of major clinical significance. Major injuries occur in only 5% of cases of blunt trauma, which implies that this study will need to prospectively evaluate 6,340 patients with blunt trauma. Consequently, study size is driven by the requirements of sensitivity. Both the derivation and validation phases of the study will need enroll sufficient patient to satisfy the sensitivity requirement, thus the entire study will need to enroll a total of 12,680 patients with blunt trauma.

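### Cases with a CT report but no intervention outcome are deleted although CT often settles their status, and the sensitivity verdict could turn on two such deletions

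*Protocol article*

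**What the plan says.** The Data analysis section fixes a complete-case rule: "Cases lacking radiographic reports or intervention outcomes will be deleted from the final data analysis". The conjunction matters, because a case with a final CT report is still dropped if its intervention outcome is missing.

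Elsewhere the outcome is built in two steps. Under Data collection and Outcome ascertainment, the final radiographic interpretation decides whether there is an injury, "but will classify injuries as major, minor, or insignificant based on review of procedural records". The Phase 1 section defines the no-injury class by the absence of injury on CT. In Table 1, diaphragmatic injuries and major pelvic fractures without intervention are minor whatever their observation status, and aortic injuries needing neither intervention nor observation are still minor.

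For the validation phase: "These values will be used to calculate point measures and 95 percent confidence intervals (CIs) for sensitivity, NPV and specificity of the decision instruments". The pass criterion is: "We will consider an instrument to be adequately validated if the lower confidence intervals for sensitivity and negative predictive value exceed 98" per cent.

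The section on the global assessment of potential missed injuries provides, for admitted patients, that "hospital discharge summaries will be reviewed in order to determine whether any SAPI were missed by the initial ED evaluation". It adds trauma, surgery and mortality logs and quality improvement records. The section on data storage provides that the link between medical record and study number is deleted at the completion of the study.

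**The concern.** The deletion rule is wider than the outcome definition requires. A patient with a negative CT needs no intervention record to be classified. Some patients with a positive CT belong to the major-or-minor outcome whatever that record would show. For the remaining CT-positive patients only the grade is unknown. All three groups are dropped.

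Two things are at stake. The first is loss of usable data. CT-negative patients supply the true-negative and false-positive cells, and hence specificity, which the article treats as the measure of potential imaging reduction. The second is the sensitivity verdict. The criterion tolerates very few misses, so a deletion rule that may be related to outcome could decide it without leaving a trace in the analysed data.

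**Working it through.** **Inputs.** Exact lower limit from the sample size section, P_L = X / (X + (N − X + 1)·F), with F the upper α/2 point on 2(N − X + 1) and 2X degrees of freedom and α = 0.05. This is the lower end of a two-sided exact 95% interval. Planned injured patients: 317 ("confirming that the instrument has 98.0% sensitivity requires studying 317 patients having injuries of major clinical significance"). Patients per phase: 6,340. Share free of all criteria: about 10%, so about 634 per phase. Pass criterion: lower limit above 98%.

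**The plan's own figure.** With X = N the limit reduces to 0.025^(1/N). Setting it to 0.98 gives N = ln(0.025)/ln(0.98) = 182.6, so 183 and not 317. The stated 317 would need a tail of 0.98^317 = 0.00165, which the article does not state. That is a separate matter. Here 317 serves only as the planned number of major injuries, and 317/0.05 = 6,340 does reproduce.

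**Sensitivity at a fixed total of 317 major injuries**

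| Data analysed | Lower limit | Result |
|---|---|---|
| 317/317, no miss | 98.84% | pass |
| 316/317, one miss | 98.25% | pass |
| 315/317, two misses | 97.74% | fail |
| 315/316, one of two misses deleted | 98.25% | pass |
| 315/315, both misses deleted | 98.84% | pass |

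If the deleted patients come on top of 317 retained true positives, the full data would be 317/318 = 98.26% (pass) with one and 317/319 = 97.75% (fail) with two, while the analysed data show 317/317 = 98.84%. Two patients are 2/317 = 0.6% of the injured and 2/6,340 = 0.03% of the phase.

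**Dependence on 317.** Two misses fail and deleting both passes for every injured total from 185 to 358. From 278 to 358, deleting one of the two is enough.

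**The opposite direction.** Deleting rule-positive injuries removes true positives and lowers the limit. With one miss the smallest passing total is 277 (276/277 = 98.005%); 275/276 = 97.998% fails. Starting from 316/317, deleting 317 − 276 = 41 true positives would turn a pass into a fail.

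**NPV.** With about 634 rule-negative patients, two misses give 98.87%, five give 98.17% and six give 97.95%. NPV fails only from six misses, so it would not reveal the problem in sensitivity.

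**Interval type.** At 315/317 a Wilson limit also fails (97.73%). A one-sided exact 95% limit (98.03%) or a Wald limit (98.50%) would pass, but the sample size section uses the exact α/2 form.

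**The case against.** A reader might infer that the rule will bias the study towards a pass. The documents do not support that, for four reasons.

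- On the primary outcome a deleted case is a miss only if it is both rule-negative and major. For most organs, major means that intervention was required, which is exactly what is unknown in these cases. No expected number is given.
- Early death is a poor example of a missing outcome, because death from the injury is itself classed as major.
- The sickest patients are mostly rule-positive: in validation an unassessable criterion counts as positive, and instability is an a priori criterion. Losing them lowers the sensitivity limit.
- The rule acts on the final database at the close of the study. It can be read as covering only cases left unresolved after investigators have reviewed ambiguous reports and the hospital course. An uninjured patient without a procedure may be recorded as having had none, and so not lack an outcome at all.

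The first three points stand and limit the claim to a vulnerability. The fourth is a possible reading, but the text does not say so. It nowhere directs that the discharge summaries and logs be used to complete a missing intervention outcome.

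The promised STARD flow diagram is relevant, but a diagram does not restore deleted cases. The comparison of enrolled with un-enrolled patients does not cover them. Further missing-data analyses may be in an analysis plan that is not shown. The point here is a rule that the article does state.

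**Conclusion.** The rule is wider than the protocol's own outcome definition supports. It discards patients whose CT already settles their class, at the expense of specificity, NPV and the major-or-minor instrument.

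For the primary sensitivity verdict it leaves an opening. At about 317 major injuries, two deleted patients who are rule-negative and truly major would change a fail into a pass; if one miss is retained in the data, a single further such deletion does so. This rests on the exact two-sided 95% limit and on an injured total between 185 and 358 for two deletions (278 to 358 for one). It does not rest on how 317 was derived. Whether such cases will occur, and in which direction any net bias would run, cannot be determined from the documents. The point merits a change of wording and one added analysis; it does not call the design into question.

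**What to change.** 1. Delete only cases with no CT report. Code CT-negative cases as no injury.
2. For CT-positive cases without an intervention record, first complete the grade from the discharge summaries, logs and quality improvement records already under review. Do this before the link to the medical record is deleted.
3. For cases still unresolved, report the complete-case result with two bounds on sensitivity and NPV. The lower bound counts rule-negative unknowns as major and rule-positive unknowns as not major. The upper bound does the reverse. For the major-or-minor instrument, apply the same bounds only where it is uncertain whether the injury is at least minor.
4. Call the instrument robustly validated only if the lower confidence limits computed on the lower-bound counts also exceed 98%.
5. Show unresolved and deleted cases by rule status in the STARD diagram.

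Counting every unresolved CT-positive case as major may look like a worst case, but it is not. Rule-positive unknowns would become true positives and raise sensitivity. A failing 315/317 (97.74%) with an assumed 42 such cases added becomes 357/359 = 98.002%, a pass.

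The cost is a revised sentence, one extra analysis and possibly a less favourable lower limit. No additional enrolment is needed.

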#### Formulation of the optimal A/P CT decision instruments

As stated previously, the primary focus of the study is to develop a decision instrument that detects injuries of major importance. Recognizing that a decision instrument that misses minor injuries will be unacceptable to some clinicians, a secondary goal of the study is to develop a decision instrument that detects all significant injuries.

To achieve these goals, we will use binary recursive partitioning to construct a combination of reliable criteria for A/P CT imaging that predicts SAPI with > 98% sensitivity, excludes significant injuries with > 98% NPV, and retains the greatest sensitivity. Each individual criterion will be viewed as a dichotomous variable. These criteria will then be used to construct the nodal points of the recursive partitions. Sensitivity will be used as the outcome measure for constructing the partitions.

We will perform two separate recursive partitioning analyses. The first partitioning will use major injury as a final outcome, while the second partitioning will focus on identifying patients with major or minor injuries. Our partitioning processes will continue until one of the following three end-points is reached. Case 1—We have isolated a subset of our criteria that identify all patients in our cohort who have significant injuries. By construction, the criteria identified in this process will have 100% sensitivity in detecting injury while retaining the highest discriminating capacity under the chi-squared analyses. In this situation we will regard the partitioning process as successful and the identified criteria will form our decision instrument(s). Case 2—We exhaust all criteria in the partitioning, but are unable to isolate a subset that captures all injured patients. In this event, we will examine the sensitivity of the combined criteria, and will regard the partitioning as successful if the lower confidence limit for the sensitivity exceeds 98%. 3—We exhaust all patients in the cohort. In this event, a limited number of criteria will predict all injuries but will not be able to discriminate between injured and uninjured patients (i.e., sensitivity of 100%, but specificity of 0%). In this case we will sequentially remove potential predictor variables (beginning with the last identified criterion) and examine the sensitivity of the remaining variables. We will regard the partitioning as successful if the lower confidence limit for sensitivity of the remaining variables exceeds 98%. We will regard the partitioning as unsuccessful if we cannot meet the lower limit threshold.

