## Abstract

Although computed tomography (CT) of the abdomen and pelvis (A/P) can provide crucial information for managing blunt trauma patients, liberal and indiscriminant imaging is expensive, can delay critical interventions, and unnecessarily exposes patients to ionizing radiation. Currently no definitive recommendations exist detailing which adult blunt trauma patients should receive A/P CT imaging and which patients may safely forego CT. Considerable benefit could be realized by identifying clinical criteria that reliably classify the risk of abdominal and pelvic injuries in blunt trauma patients. Patients identified as “very low risk” by such criteria would be free of significant injury, receive no benefit from imaging and therefore could be safely spared the expense and radiation exposure associated with A/P CT. The goal of this two-phase nationwide multicenter observational study is to derive and validate the use of clinical criteria to stratify the risk of injuries to the abdomen and pelvis among adult blunt trauma patients. We estimate that nation-wide implementation of a rigorously developed decision instrument could safely reduce CT imaging of adult blunt trauma patients by more than 20%, and reduce annual radiographic charges by $180 million, while simultaneously expediting trauma care and decreasing radiation exposure with its attendant risk of radiation-induced malignancy. Prior to enrollment we convened an expert panel of trauma surgeons, radiologists and emergency medicine physicians to develop a consensus definition for clinically significant abdominal and pelvic injury. In the first derivation phase of the study, we will document the presence or absence of preselected candidate criteria, as well as the presence or absence of significant abdominal or pelvic injuries in a cohort of blunt trauma victims. Using recursive partitioning, we will examine combinations of these criteria to identify an optimal “very low risk” subset that identifies injuries with a sensitivity exceeding 98%, excludes injury with a negative predictive value (NPV) greater than 98%, and retains the highest possible specificity and potential to decrease imaging. In Phase 2 of the study we will validate the performance of a decision rule based on these criteria among a new cohort of patients to ensure that the criteria retain high sensitivity, NPV and optimal specificity. Validating the sensitivity of the decision instrument with high statistical precision requires evaluations on 317 blunt trauma patients who have significant abdominal-pelvic injuries, which will in turn require evaluations on approximately 6,340 blunt trauma patients. We will estimate potential reductions in CT imaging by counting the number of abdominal-pelvic CT scans performed on “very low risk” patients. Reductions in charges and radiation exposure will be determined by respectively summing radiographic charges and lifetime decreases in radiation morbidity and mortality for all “very low risk” cases.

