## Objectives

### General design

In this prospective, cohort, multi-center study we seek to develop an imaging decision tool that will enable clinicians to identify patients with blunt trauma who are at “very low-risk” for clinically significant A/P injuries. Implementation of the decision tool will require clinicians to assess the presence or absence of specific clinical findings. Patients with a full assessment of all criteria and who exhibit none of the clinical findings will be designated as “very low-risk”. Patients who exhibit one or more of the clinical findings, as well as those for whom a complete assessment of criteria cannot be completed, will be designated as “not low-risk.” Patients who are designated as very low-risk will have negligible potential to harbor significant A/P injuries, will receive no benefit from A/P CT imaging, and will therefore be safe to exclude from A/P CT imaging. All other patients remain candidates for imaging. It is worth noting that while our project focuses on developing a rule for combined A/P CT imaging, the rule will also be suitable for evaluating patients for isolated abdominal or isolated pelvic imaging. This is a reflection of the fact that patients who are designated as low risk by our instrument will have negligible risk of either abdominal or pelvic injury, and can safely be excluded from abdominal-pelvic imaging, isolated abdominal imaging, or isolated pelvic imaging.

Classification by an optimal decision instrument will reflect a balance between the risk of imaging (malignant transformation from exposure to ionizing radiation), the costs of CT, and the risks of not imaging (potential harm from unrecognized significant injuries). Because the rate of lethal malignant transformation is low, the decision tool must exhibit high sensitivity to ensure that the missed injury rate is very low, and that virtually all patients with significant injuries are designated as “not low risk.”

To be clinically useful, the decision tool must also assign low-risk classification to as many uninjured patients as possible. This is equivalent to requiring the tool to produce as few false positive results as possible, or equivalently, exhibit high specificity. The proportion of patients who can safely be spared imaging is directly related to the instrument’s specificity, so the development process will focus on identifying a tool with the highest possible specificity.

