We will assign a final clinical outcome for each patient based on the results of A/P CT imaging as well as the patient’s hospital course. Patients who we designate as having injuries must have injuries evident on CT imaging. This reflects the fact that if injuries are not apparent on CT imaging, it is immaterial whether the patient underwent such imaging. Furthermore, we will classify each patient as having, in order of increasing severity: 1—no injuries (no injuries evident on CT); 2—insignificant injuries (e.g., minor bruising, small hematomas, or isolated small avulsion fractures); 3—clinically minor injuries (significant injuries that require no specific intervention); and 4—clinically major injuries (significant injuries that require specific intervention or result in patient death). Our final outcome classification will be based on the most severe type of injury sustained by each patient. We will concatenate our final outcome assignments with the criterion assessments to create our final analysis database.

We will apply chi-squared binary recursive partitioning to this data set to identify separate combinations of criteria that identify both major and minor significant abdominopelvic injuries with > 98% sensitivity and > 98% NPV, assuming such combinations exist. If more than one combination of variables exhibits the requisite sensitivity and negative predictive values for injury, the combination with the highest specificity will be adopted as the optimal low-risk decision instruments.

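### The derivation section gives inconsistent rules for choosing the decision instrument: highest specificity in some places, greatest or 100% sensitivity in others, with more than one partitioning measure and success bar

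*Protocol article*

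**What the plan says.** **Objective.** Phase 1 (Derivation) looks for combinations that "identify both major and minor significant abdominopelvic injuries with > 98% sensitivity and > 98% NPV, assuming such combinations exist". If several qualify, "the combination with the highest specificity will be adopted as the optimal low-risk decision instruments". The Abstract agrees: the chosen subset "retains the highest possible specificity and potential to decrease imaging". So does General design: "the development process will focus on identifying a tool with the highest possible specificity".

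The section Formulation of the optimal A/P CT decision instruments sets the same two thresholds but ends differently: the combination "excludes significant injuries with > 98% NPV, and retains the greatest sensitivity".

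**Partitioning measure.** Phase 1 specifies chi-squared binary recursive partitioning, and Case 1 in Formulation also refers to chi-squared discrimination. Between them, Formulation states: "Sensitivity will be used as the outcome measure for constructing the partitions".

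**Stopping and success.** Formulation gives three end-points.
- Case 1: "We have isolated a subset of our criteria that identify all patients in our cohort who have significant injuries". This counts as success and the subset becomes the instrument.
- Case 2: the criteria run out before all injured patients are captured. The plan "will regard the partitioning as successful if the lower confidence limit for the sensitivity exceeds 98" percent.
- Case 3: the patients run out, so sensitivity is 100% and specificity 0%. Criteria are then removed from the last one backwards, and the same lower-limit test on sensitivity applies.

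None of the three cases mentions NPV. The validation section requires lower limits above 98% for both sensitivity and NPV. Nothing says which statement prevails.

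**The concern.** This rule determines which instrument leaves derivation and is then tested in a second cohort of 6,340 patients. General design ties the share of patients spared CT directly to specificity.

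Two analysts following different sections could derive different instruments from the same data. One would look for the leanest rule above a 98% floor. The other would keep adding criteria until the last injured patient is caught. An instrument that qualifies under one section may also fail the bar in the other. With the rule open, the choice could be made after the derivation results are seen.

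**Working it through.** **1. Why the objectives oppose each other.** General design and Core methods class a patient as not low-risk if any criterion is present. For criteria sets A ⊂ B, every patient positive under A is positive under B, so
- sensitivity(B) ≥ sensitivity(A)
- specificity(B) ≤ specificity(A)

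Maximising sensitivity favours more criteria. Maximising specificity above a floor favours fewer.

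**2. The sections side by side.**

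| Place | Objective | Partition on | Sensitivity bar | NPV bar |
|---|---|---|---|---|
| Phase 1 | highest specificity | chi-squared | > 98%, no limit named | > 98%, no limit named |
| Formulation, opening | greatest sensitivity | sensitivity | > 98%, no limit named | > 98%, no limit named |
| Formulation, Case 1 | capture all injured | chi-squared | 100% observed | none |
| Formulation, Cases 2 and 3 | none stated | – | lower limit > 98% | none |
| Validation | – | – | lower limit > 98% | lower limit > 98% |

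**3. The plan's own figure.** The sample size section gives P_L = X / (X + (N − X + 1)·F), with α/2 = 0.025. With no misses (X = N) this equals 0.025^(1/N).
- Setting P_L = 0.98 gives N = ln 0.025 / ln 0.98 = 182.6, so 183. The stated 317 is not reproduced. That is a separate matter; 317 is used below only as the planned number of major injuries per phase.
- At N = 317 with no misses, P_L = 0.025^(1/317) = 98.84%.

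**4. How many misses each bar allows.** The same exact limit, with 317 injured:

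| Misses | Sensitivity | Lower 95% limit | Point > 98% | Limit > 98% |
|---|---|---|---|---|
| 0 | 100% | 98.84% | yes | yes |
| 1 | 99.68% | 98.26% | yes | yes |
| 2 | 99.37% | 97.74% | yes | no |
| 6 | 98.11% | 95.93% | yes | no |
| 7 | 97.79% | 95.50% | no | no |

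The bars therefore allow 6 misses (point estimate), 1 (lower limit) or 0 (Case 1). A rule with 2 to 6 misses passes the first and fails the second.

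**5. Case 1 with fewer injured patients.** Case 1 attaches no limit. With no misses the lower limit is 98.004% at 183 injured and 97.99% at 182. Below 183, Case 1 would declare success although the limit does not exceed 98%.

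**6. Does the missing NPV check matter?** By the same formula, a lower NPV limit above 98% needs at least 183 low-risk patients with no misses, or 277 with one. The plan assumes about 10% of patients are free of the criteria, which is 634 of 6,340. One miss among 634 gives a lower NPV limit of 99.12%. At the planned numbers the omission changes nothing. It would matter only if the low-risk group fell below 183/6,340 = 2.9% (no misses) or 277/6,340 = 4.4% (one miss).

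**7. What specificity is worth.** Each phase has 6,340 − 317 = 6,023 patients without major injury, so one percentage point of specificity is about 60 patients. The article gives no frequencies for the criteria, so the number of points at stake cannot be computed.

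**The case against.** - **The slip.** The phrase about greatest sensitivity is very likely a typing error. Its sentence has already set a sensitivity threshold, and it parallels the Abstract's sentence, which ends on specificity. This stands. A reader might infer three separate, mutually incompatible rules, but the document does not support that: greatest sensitivity and the Case 1 stop coincide whenever 100% is attainable. Correcting the word still leaves two partitioning measures, the Case 1 stop and the differing bars.
- **Specificity is not ignored.** A reader might infer that Formulation never considers it. That is too strong. Chi-squared splits reward separation of injured from uninjured patients, and Case 3 gives up sensitivity because specificity is zero. But Case 1 compares no qualifying subsets, and Case 3 acts only at the extreme.
- **Verdicts differ only in some situations.** With 317 injured and no misses, observed sensitivity and NPV are both 100% and the lower sensitivity limit is 98.84%, so every sensitivity bar is met. The 2-to-6-miss conflict also requires reading the unqualified 98% as a point estimate. Those sentences name no limit, while Cases 2 and 3, the validation section and the sample size section do attach 98% to one. The reading is open.
- **Zero misses is a defensible margin.** If a one-miss bar yields a rule whose true sensitivity is 316/317, the chance of at most one miss among 317 at validation is (316/317)^317 + (316/317)^316 ≈ 0.74. At 315/317 it is about 0.41. This stands as a reason to leave the bar to the sponsor.
- **Validation protects the result.** Its criterion is unambiguous and applied to new patients, so this ambiguity cannot by itself produce a falsely validated rule. It affects which rule is tested and how much imaging that rule could spare.

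**Conclusion.** The derivation rule is inconsistent as written and needs correcting. The core conflict is highest specificity above a 98% floor (Abstract, General design, Phase 1) against greatest or 100% sensitivity (Formulation). Two partitioning measures and non-matching success bars add to it.

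The conflict in objective follows from the any-positive definition and needs no assumption about the data. The sections can select different instruments; they need not do so in every data set.

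The gap in bars is 6, 1 or 0 allowed misses. It rests on 317 injured patients, the protocol's exact two-sided 95% limit, and the point-estimate reading of the unqualified threshold. If that threshold means a lower limit, the gap narrows to 1 against 0. The secondary instrument (major or minor injury) will have more injured patients and different counts.

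A reader might also infer a particular loss of specificity, or that recursive partitioning is the wrong method. Neither is supported. Any specificity figure would rest on assumed criterion frequencies, and partitioning is a legitimate prespecified choice, although stepwise splitting does not guarantee the subset with the highest specificity.

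**What to change.** 1. In the opening of Formulation, change the end of the sentence from greatest sensitivity to highest specificity.
2. Name one partitioning measure and use it in Phase 1 and throughout Formulation.
3. State one derivation bar for sensitivity and NPV and apply it in Phase 1 and in all three cases. Either use the lower 95% limit above 98% already required at validation, or a zero-miss bar if the sponsor wants that safety margin.
4. Among subsets meeting that bar, adopt the one with the highest specificity, in Case 1 as well.

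An optional check is to compare all any-positive subsets of the nine criteria found reliable in the preliminary work: 2^9 − 1 = 511 subsets, which takes negligible computing. This would sit beside recursive partitioning and need not replace it.

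The cost is wording only, with no change to sample size or data collection. If the bar allows one miss, derivation optimism is somewhat greater than with a zero-miss stop and the margin at validation is smaller. The sponsor should make that choice explicitly before derivation data are analysed.
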